#### Subgroup analysis

It is uncertain whether delaying the administration of a first dose of pertussis-containing vaccine affects the subsequent risk of developing atopic sensitisation or atopic diseases, with observational studies variously reporting a deleterious [34], beneficial [35–37], and no effects [38]. However, to the best of our knowledge, the relationship between atopic outcomes and age at vaccination has only been tested in recipients of the same type of vaccine, but not in a population vaccinated with a first dose of either, wP or aP. In order to explore possible modification of the effect of the immunisation with wP vs aP by age at vaccination, we will carry out subgroup analyses according to the age of the first dose of wP or aP (before or at 90 days of age, or after 90 days of age).

## Bias

The most likely potential sources of bias are described using the Risk Of Bias In Non-randomised Studies-of Interventions (ROBINS-I) framework [39].

### Pre-exposure domains

#### Bias due to confounding

Calendar date of birth, and state of birth are likely to be associated with one or more of the atopic disease outcomes of interest, either through a direct effect on the disease or through an effect on healthcare utilisation conditional upon disease. They are also known predictors of vaccination with wP versus aP during the transition to aP routine vaccination (Figs 3 and 4). Models will therefore be stratified by state of birth and adjusted for date of birth.

**Fig 3 pone.0260388.g003:**
[figure not shown]
Direct acyclic graph before adjustment by confounders and baseline covariates. The blue node represents the exposure (wP or aP); orange and grey nodes: Perinatal, environmental and biological factors at birth/before the exposure that may influence the outcome of interest, but not the receipt of the study vaccines; brown nodes: Confounders of the association between the exposure and atopic asthma; yellow nodes: Adjusted variables; white node: Outcome of interest. Because the association between low birthweight and asthma is mainly driven by gestational age at delivery, birthweight is not depicted in this diagram [40]. C-section: Birth by caesarean. Data are available for all the nodes except for those in orange.

**Fig 4 pone.0260388.g004:**
[figure not shown]
Direct acyclic graph after adjustment by confounders and baseline covariates. The blue node represents the exposure (wP or aP); orange and grey nodes: Perinatal, environmental and biological factors at birth/before the exposure that may influence the outcome of interest, but not the receipt of the study vaccines; brown nodes: Confounders of the association between the exposure and atopic asthma; yellow nodes: Adjusted variables; white node: Outcome of interest. Because the association between low birthweight and asthma is mainly driven by gestational age at delivery, birthweight is not depicted in this diagram [40]. C-section: Birth by caesarean. Data are available for all the nodes except for those in orange.

Age is associated with the risk of various atopic diseases, and while it is also associated with vaccination, it should not be associated with receipt of wP versus aP after controlling for date of birth; nonetheless, the Cox survival model intrinsically controls for any effect of age on the risk of outcomes [31].

Statistical models will be adjusted for socioeconomic index, accessibility or remoteness index, Aboriginal ethnicity (identified through a validated multi-stage median algorithm) [41], season of birth and birth order (i.e. the relative position of a child in relation to their siblings). These variables are plausibly associated with the atopic outcomes of interest, and might also be systematically different between children vaccinated with wP versus aP (Figs 3 and 4).

The prevalence of childhood asthma among Aboriginal and/or Torres Strait Islander people (hereafter respectfully referred as Aboriginal) has been measured by a number of surveys across different settings. According to the most recent National Aboriginal and Torres Strait Islander Health Survey (2018/2019), the prevalence of current and long-term asthma in children under 15 years old was similar for Aboriginal (11.5%; 95% CI 9.6% to 13.4%), and non-Aboriginal children (9.7%; 95% CI 8.5 to 10.9%) [42]. Older studies suggested Aboriginal children living in extremely remote WA may have a lower incidence of asthma across their life course (7.3%; 95% CI 5.3% to 9.7%) than those living in metropolitan Perth (30.5%; 95% CI 27.3% to 33.8%) [43].

Compared to non-Aboriginal Australians, Aboriginal Australians are more likely to experience chronic poverty during their lifespan, intergenerational trauma, smoking during pregnancy, and poor birth outcomes such as prematurity and low-birth-weight newborns [43]. Therefore, any difference in risk of asthma among Aboriginal and non-Aboriginal children may be mediated through differences in socioeconomic status. In the proposed analysis, we intend to adjust for both socioeconomic and Aboriginal status.

The linked datasets do not contain information on some potentially important predictors of asthma or other atopic diseases, including parental and family history, second-hand smoke exposure, maternal obesity, gestational weight gain, or breastfeeding status. However, insofar as these variables are very unlikely to predict the vaccine type received (i.e. they are not likely to be confounders), failure to adjust for them is not expected to bias the effect estimates.

Maternal smoking during pregnancy is captured in the perinatal datasets, and is likely to be a proxy for second-hand smoke exposure. Adjustment for this prognostically important covariate may improve the precision of our effect estimates.

The *sibling effect* refers to the protection against the development of atopic diseases conferred by having siblings. This concept was described for the first time in a cross-sectional analysis from the British Birth Survey in 1986, as cited by Karmaus et al [44], and thought to be related to the hygiene hypothesis proposed by Strachan in 1989 [45].

The representations of the sibling effect in the literature vary widely and include birth order, the size of the sibship, or the number of brothers [46]. Although this phenomenon is supported by a number of epidemiologic studies, its underpinning mechanisms are not well understood. Briefly, increased birth order has been proposed as a proxy of frequent exposure to microorganisms, which are transmitted through unhygienic contact with older siblings during early childhood [45]. These include airway pathogens with Th_1_ and Th_17_ polarising properties, that are speculated to shift the infant’s Th_2_-biased *in utero* immunophenotype, towards allergy protective immune responses [47]. However, the sibling effect may also be a consequence of *in utero* immune programming from previous pregnancies. For example, increased birth order has been associated with lower levels of IgE in cord blood, and possibly with a lower risk of atopic sensitisation [44].

During the period of transition to aP-only doses, the receipt of wP or aP as a first dose of the primary series should have been driven by their availability in primary care centres only. Nonetheless, it is reasonable that parents would have requested the preferential administration of aP vaccine if a previous child (sibling) experienced any adverse reaction following vaccination with wP. Due to the possibility of confounding, we will include the number of previous pregnancies (a surrogate of birth order) as a variable in the models.

In addition, residual confounding that may lead to biased estimates will be approached using injury, trauma and poisoning-related ICD codes, as negative control outcomes (Table 1).

#### Bias in selection of participants into the study (collider bias conditioning enrolment on survival)

Collider bias arises from conditioning on a common effect of the exposure and the outcome [48]. This type of bias can emerge through the process of selecting individuals into the analysis (i.e. selection bias) [48].

There are two potential sources of bias by delaying cohort entry, or failure to synchronise the start of follow-up with the time of exposure (i.e. first dose of pertussis-containing vaccine).

Firstly, if there exists a causal effect which is different among younger and older children, any effect measured in older children will be systematically different from the overall effect. Secondly, bias could theoretically occur if vaccination of wP versus aP impacts on the likelihood of children surviving to cohort entry. For example if wP vaccine is less effective than aP for preventing death from pertussis disease. In the absence of any causal relationship between pertussis vaccine and atopic disease, the cohort of survivors at 5 years old will be relatively depleted of wP-vaccinated children (who are more likely to have died from pertussis) and those with atopic disease (who are more likely to have died from anaphylaxis) before cohort entry; children who are both wP-vaccinated and who also have atopic disease will be especially unlikely to survive to cohort entry. As a result of this depletion, atopic diseases will be less common among wP vaccinated than aP vaccinated children who survive to cohort entry, even though wP has no protective effect. Nonetheless, in our context, infant and child mortality rates are very low and deaths from pertussis or atopic diseases are rare, so any collider bias is presumably negligible. Assuming no residual confounding, effect estimates are likely to be accurate from the chosen time zero until the end of follow-up. The same explanation applies to conditioning enrolment on survival at 8 years old.

### At-exposure domain

#### Bias in classification of the exposure

Although the accuracy of the AIR is difficult to validate, by 2001 the underestimation of the immunisation coverage was between 2.7 and 5% [49], suggesting that some vaccine doses were not ascertained.

While it is plausible that some doses of aP were mis-recorded as wP (and vice versa), there is no reason to expect that errors in classification of the vaccine received are differential with respect to ascertainment of the outcomes of interest, since the latter occurred after the exposure, and were recorded through independent mechanisms. As such, any misclassification of vaccination status is likely to bias toward a null effect.

### Post-exposure domains

#### Bias due to missing data (selection bias)

The available administrative data do not identify whether a child emigrated from the state of birth. Therefore, hospital encounters that occurred outside of NSW and WA will not be ascertained. For those children who migrated overseas, data may also be missing for one or more doses of pertussis-containing vaccine. However, as cited by Gidding et al [22], in 2011 just 1.2% of the residents of NSW and WA migrated interstate, and 0.8% migrated overseas. In either case, the rates of interstate migration or emigration from Australia are unlikely to be different for wP versus aP vaccinated children.

According to the 2016 Australian Census, 34.5% and 39.7% of the population of NSW and WA was born overseas, respectively [50,51]. Because the chosen cohort only includes children born in NSW or WA, findings from this study might not be generalisable to immigrant children living in these jurisdictions [22].

#### Bias in measurement of the outcome (information bias)

Concerns regarding the changes of anaphylaxis-related hospitalisation codes, their impact on epidemiologic trends, and further incomplete identification of anaphylaxis cases have been described everywhere else [52], Our study will only ascertain hospitalisations or emergency department presentations where severe IgE-mediated hypersensitivity is implied (i.e. anaphylactic shock) or those labelled as anaphylactic reaction. We expect our approach will be specific for IgE-mediated disease outcomes, but at the expense of sensitivity. Therefore, the proposed analysis plan is unlikely to fully capture the burden of IgE-mediated atopic disease morbidity since many mild cases would not have been hospitalised, or may have received alternative codes [13].

Furthermore, random errors in the identification of the outcome might be possible since ICD codes were used to determine hospitalisations for asthma and other atopic diseases. Any misclassification of the outcome will be non-differential and likely to bias toward the null. Likewise, presentations to the emergency department for the outcomes of interest may be miscoded, as diagnoses are primarily ascribed by clinical and clerical personnel at the emergency facilities who are not specialised in clinical coding.

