## Introduction

Conventional whole-cell pertussis vaccines (wP) were developed between the 1920s and 1940s [1], with subsequent widespread use in combination with diphtheria and tetanus toxoids as a three-dose primary schedule. The reactogenicity of these formulations is thought to be largely driven by the presence of endotoxin, and may manifest as self-limited injection site reactions, fever, irritability and other systemic symptoms [2,3].

The implementation of wP-based primary series in the past century successfully contributed to the near elimination of pertussis in countries like Australia which achieved high immunisation coverage [4]. From 1974, improved access to wP formulations through the Expanded Programme of Immunization has decreased vaccination inequalities in the developing world and the global burden of pertussis disease in children younger than 5 years old [5]. Nevertheless, geographical, social factors and weak health systems still drive vaccine inequity within low and middle income countries, substantially affecting the coverage of the first and third dose of pertussis vaccine primary series, and pertussis-related deaths [5,6]. Development of acellular subunit vaccines (aP) in the 1980s with substantially reduced endotoxin content and improved reactogenicity profile [7], prompted the switchover to aP primary immunisation in most high-income countries over the past 25 years.

In Australia, the transition from wP to exclusive use of aP vaccine formulations for the primary series occurred during the period of 1997 to 1999 [4]. During this period, existing batches of wP were used and fully depleted by community vaccine providers, before being replenished with batches of aP vaccine. This process occurred in a more-or-less stochastic fashion through the jurisdictional immunisation programs. Therefore, the receipt of wP or aP on the day of the first vaccination was not driven by the individual preference of carers or providers, but by which vaccine happened to be available at the primary care services and public immunisation clinics.

The period of switchover from wP to aP in Australia also overlapped with the change from the ninth to the tenth revision of the International Classification of Diseases (ICD) coding scheme. The first edition of ICD-10 AM (AM: Australian Modification) was introduced in New South Wales (NSW) in July 1998, and in Western Australia (WA) in July 1999 [8].

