## Methods

### Study design

The analysis plan described in this protocol is part of a larger project, that aimed to assess Australia’s National Immunisation Program using probabilistic linked data for 1.95 million children born in WA or NSW between 1996 and 2012, encompassing perinatal, birth registries and hospital data, as well as Commonwealth data collections from the Australian Immunisation Register (AIR)—known as Australian Childhood Immunisation Register or ACIR before 2016—and National Death Index. The details of the record linkage procedures have been published elsewhere [22,23].

The cohort for this study will be restricted to all live births in WA or NSW between 1 January 1997 and 31 December 1999. These will be sourced from state birth registries and perinatal data collections (WA Midwives’ Notification System and NSW Perinatal Data Collection) using the above-described linked dataset. The assembled information includes the parent and child’s demographics, maternal obstetric and medical history, labour and delivery details, hospital admissions and presentations to the emergency departments. Hospitalisation data are linked for analysis for the period of January 1997 to December 2013 (WA), and July 2001 to December 2013 (NSW). Presentations to the emergency departments are available from all hospitals in WA from January 2002 to December 2013, and from most public hospitals located in the metropolitan areas of NSW from January 2005 to December 2013 [22].

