#### Outcomes

Admissions to hospital for asthma, all-cause anaphylaxis, food anaphylaxis, anaphylactic reaction to *Hymenoptera* stings (hereafter referred as venom), all-cause urticaria, atopic dermatitis and ‘allergy’ will be ascertained from the WA Hospital Morbidity Data Collection and the NSW Admitted Patient Data Collection.

These datasets contain the dates of admission and separation (i.e. discharge, transfer or death), the primary diagnosis and codes for diagnostic procedures performed during hospital stay [22]. In addition, up to 20 secondary diagnoses for children born in WA, and up to 50 secondary diagnoses for children born in NSW are also provided [22]. Clinical diagnoses were coded using the ICD system (ICD-9 CM and ICD-10 AM) [22]. These diagnostic codes are listed in Table 1.

**Table 1 pone.0260388.t001:** ICD-9 CM and ICD-10 AM diagnostic codes of interest.

Outcome	ICD-9 CM codes	ICD-10 AM codes
Asthma	493, 493.0, 493.00, 493.01, 493.02, 493.1, 493.10, 493.11, 493.12, 493.82, 493.2, 493.8, 493.9, 493.90, 493.91, 493.92	J45, J45.0, J45.1, J45.9, J45.8, J46
All-cause anaphylaxis	995.0, 995.6, 995.60, 995.61, 995.62, 995.63, 995.64, 995.65, 995.66, 995.67, 995.69, 995.4, 989.5	T78.2, T78.0, T63.4, T88.6, T88.2
Food anaphylaxis	995.6, 995.61, 995.62, 995.63, 995.64, 995.65, 995.66, 995.67, 995.69	T78.0
Venom	989.5	T63.4
Urticaria	708, 708.0, 708.1, 708.2, 708.3, 708.4, 708.5, 708.8, 708.9	L50, L50.0, L50.1, L50.2, L50.3, L50.4, L50.5, L50.8, L50.6, L50.9
Atopic dermatitis	691.8	L20.0, L20.8, L20.9
Allergy	995.3	T78.4
Combined injury, trauma and poisoning	800 to 999, excluding 995, 978, 979	S00 to T98 excluding, T78.0, T78.2, T78.3, and T78.4

For the purpose of this study, we will only include for analysis the primary diagnosis.

*Hospitalisations for asthma after 5 years old*. Every eligible child at time zero (i.e. alive at the start of follow-up, and vaccinated with a first dose of wP or aP between 39 and 111 days old) will be included in the cohort. Where the outcome of interest is time-to-first admission to hospital for asthma after 5 years old, time zero will be the date of the fifth birthday; hospitalisations for asthma before 5 years old will be disregarded. The same rules will be applied to the time-to-recurrent event analyses.

The reasons for only including hospitalisations for asthma after 5 years of age are twofold.

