Firstly, the molecular phenotypes of children with acute exacerbations of wheezing differ according to the expression of type I interferon signatures [25]. The latter have been found to be upregulated in children with wheezing episodes triggered by respiratory virus infection, but in contrast, respiratory virus negative exacerbations are characterised by the upregulation of Th_2_ associated pathways, downregulation of interferon gamma and increased likelihood of admission to hospital [25]. Unlike asthma in older children, a large proportion of wheezing episodes in preschool aged children are thought to be non-IgE mediated inflammation triggered by respiratory virus infection rather than Th_2_–mediated inflammation and airway hyperresponsiveness, and are unlikely to be prevented by wP priming.

Second, hospitalisation data for children born in NSW are only available from July 2001 and therefore, the follow-up period between the first dose of wP or aP and this time point is not available.

Admissions to hospital with asthma-related ICD codes (primary diagnosis) occurring within 14 days will be considered the same episode. Those occurring after 14 days from the previous admission will be defined as recurrent episodes.

*Hospitalisations for other atopic outcomes*. For atopic outcomes other than asthma, children born in WA will enter the cohort at 4 months old (time zero), and those born in NSW will enter the cohort at 5 years old.

Hospitalisation for the same atopic outcome occurring within 14 days will be considered the same episode of illness. Those occurring after 14 days from the previous admission will be defined as a recurrent event.

*Emergency department presentations*. For children born in WA, presentations to the emergency department for asthma and other atopic outcomes will be ascertained from the WA Emergency Department Data Collection [22], using a diagnostic hierarchy rule based on data availability, where the most specific diagnostic category is chosen over the less specific [26]. According to this rule, outcome data will be determined from the following sources: diagnosis (ICD code), symptom code, diagnosis at discharge, presenting complaint and major diagnosis category. These data are available from January 2002 to December 2013 and therefore, every model will be fitted using the date of the fifth birthday as the entry date to the cohort.

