#### Hospitalisations for other atopic outcomes

We will compare rates of admission for all-cause anaphylaxis, food anaphylaxis, venom, urticaria and atopic dermatitis by means of unadjusted and adjusted Cox regression models for the time-to-first event [31], and Andersen-Gill models for recurrent events using robust standard errors to account for within-child dependence [32]. For children born in WA, the cohort entry will be set at 4 months old, and vaccination status will be treated as a time-dependent covariate. For children born in NSW, the cohort entry will be set at 5 years old. Censoring rules will be applied as above.

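### Outcome misclassification is declared non-differential without condition, but for WA non-asthma admissions, which span the July 1999 ICD change, this holds only given age and an adequate date-of-birth adjustment

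*Protocol article*

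**What the plan says.** The section on bias in measurement of the outcome concludes: "Any misclassification of the outcome will be non-differential and likely to bias toward the null". It sets no condition on outcome, state, period or model.

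Other sections of the protocol article bear on this:

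- **Introduction.** "The period of switchover from wP to aP in Australia also overlapped with the change from the ninth to the tenth revision" of the ICD. The change is dated "in Western Australia (WA) in July 1999" and, for NSW, July 1998.
- **Study design.** The cohort is "restricted to all live births in WA or NSW between 1 January 1997 and 31 December 1999". WA admissions are linked from January 1997, NSW admissions from July 2001.
- **Hospitalisations for other atopic outcomes.** "For children born in WA, the cohort entry will be set at 4 months old". Both unadjusted and adjusted Cox models are planned.
- **Outcomes, asthma.** Here "time zero will be the date of the fifth birthday".
- **Bias due to confounding.** Birth date and state are named as predictors of wP versus aP and as possible influences on healthcare use. Models are to be stratified by state and adjusted for date of birth. The Discussion repeats that these two predictors will be controlled.
- **Table 2.** The variables footnoted for the models include season of birth. Date of birth is not in the table.

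**The concern.** At a given age in early childhood, an earlier-born WA child is coded in ICD-9 CM and a later-born one in ICD-10 AM. Because birth date also predicts the vaccine received, coding version is associated with exposure. If the two code sets capture a different share of true cases, the recorded event rate differs between the vaccine groups unless birth date is handled. The error can then go in either direction, not only toward the null.

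The exposed analyses matter. WA from 4 months is the only admission follow-up in the study that covers the first years of life, where food anaphylaxis and atopic dermatitis admissions lie closest to the food-allergy hypothesis. A blanket toward-the-null statement invites readers to treat any protective estimate there as conservative.

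**Working it through.** The article gives no figure for this bias, so there is none to reproduce. The check has four steps.

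**1. Which follow-up spans the change.** Months under ICD-9 CM = time from entry (birth + 4 months) to 30 June 1999.

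| WA birth date | Entry | Months under ICD-9 CM |
|---|---|---|
| 1 Jan 1997 | 1 May 1997 | 26 |
| 1 Jan 1998 | 1 May 1998 | 14 |
| 1 Jul 1998 | 1 Nov 1998 | 8 |
| 1 Mar 1999 or later | 1 Jul 1999 or later | 0 |

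The earliest-born children are 30 months old on 1 July 1999, so both versions coexist only between ages 4 and 30 months. Asthma follow-up starts at age 5, so no earlier than 1 January 2002. NSW admissions start in July 2001. Emergency data start in 2002 (WA) and 2005 (NSW). All of these begin after the change.

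**2. Conditional and marginal association.** With entry fixed at 4 months, time since entry is age minus a constant. Age and birth date together fix the calendar date and hence the ICD version. Two children of the same age and birth date share a version whatever vaccine they had, so the error is non-differential conditional on both. Without birth date it is not.

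**3. Size when there is no vaccine effect.** These assumptions are not in the documents:

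- the wP share falls as a logistic curve in birth date (midpoint 20 or 26 months after January 1997, scale 2 to 5 months);
- the hazard is flat, early or infant-peaked by age;
- the capture ratio r (recorded rate under ICD-9 relative to ICD-10) is 0.7 or 1.3, with 0.5 as an extreme.

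Expected hazard ratios come from a Poisson model on expected counts with one term per month of age, which is equivalent to Cox for rare first events. Under the assumed curves, 7.0-8.6% of wP person-time and 0.4-1.6% of aP person-time falls under ICD-9.

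| r | No birth-date term | Linear birth date | Spline (df 5) |
|---|---|---|---|
| 0.7 | 0.866-0.981 | 0.972-1.007 | 0.999-1.001 |
| 1.3 | 1.019-1.129 | 0.996-1.027 | 1.000 |
| 0.5 (extreme) | 0.774-0.967 | 0.953-1.014 | 0.998-1.001 |

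A month-of-birth factor gives 1.000 throughout.

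**4. Hand check of the unadjusted column.** The unadjusted ratio is close to (1 − (1 − r)s_wP) / (1 − (1 − r)s_aP), where s is the share of true events falling under ICD-9. In the most affected case (midpoint 20, scale 2, infant-peaked) the captured fractions at r = 0.5 are 0.750 and 0.968. Hence s_wP = 0.250/0.5 = 0.50 and s_aP = 0.032/0.5 = 0.064.

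- r = 0.7: 0.850/0.981 = 0.866
- r = 1.3: 1.150/1.019 = 1.129
- r = 0.8: 0.900/0.987 = 0.912

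In the least affected case (flat hazard, s = 0.080 and 0.016), r = 0.8 gives 0.984/0.997 = 0.987. An assumed 80% capture therefore means about 0.91-0.99 unadjusted.

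**The case against.** The strongest reply is that the plan already deals with this. The confounding section commits to adjustment for date of birth and recognises that birth date may act through healthcare use. Step 3 shows that a flexible term removes the bias and that even a linear one leaves little. This stands, and it sets the limit on the point. It does not rescue the sentence, because the sentence carries no such condition, Table 2 omits date of birth from the model variables, the form of the term is not fixed (p-splines are offered only where required, under the asthma analysis), and unadjusted estimates will also be reported.

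A second reply is that the sentence follows a remark about random errors, while changes in anaphylaxis codes are raised at the start of the same section. That is a fair reading of intent, but the sentence says any misclassification.

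Third, Table 1 lists codes for each outcome in both versions, so the capture difference may be small. That is true, and neither its size nor its direction is documented. The mapping is not perfectly parallel: 995.60 is listed under all-cause but not under food anaphylaxis. This may be a slip and settles nothing about direction.

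Fourth, at a fixed age, stratifying on coding version amounts to dichotomising birth date, which is coarser than the planned adjustment. That is why stratification should be added to the birth-date term and not replace it.

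A reader might also infer that the hazard ratio would be off by the whole capture ratio, for example 0.80 at 80% capture, close to the motivating odds ratio of 0.77. The documents do not support this. That figure compares a child coded wholly in ICD-9 with one coded wholly in ICD-10, which no planned model does. Follow-up runs to age 15 or December 2013, with at most 26 months under ICD-9.

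**Conclusion.** The point holds as a limited one. For WA non-asthma admissions, misclassification is non-differential only conditional on age and an adequate date-of-birth adjustment. The unconditional statement is unsupported for the unadjusted models, and for adjusted models if Table 2 is the full covariate list.

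With assumed relative capture of 70-130%, a true hazard ratio of 1 becomes roughly 0.87-1.13 unadjusted, 0.97-1.03 with linear birth date and about 1.00 with a spline. An unadjusted value near 0.77 needs 50% capture together with an infant-peaked hazard. All of these figures rest on assumed capture ratios, vaccine transition curves and hazard shapes. Two stronger conclusions do not follow: that the plan has no safeguard, or that wP will look protective.

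**What to change.** 1. **Wording.** In the outcome-measurement section, say that for WA non-asthma admissions misclassification may differ by vaccine type, in either direction, unless date of birth or coding era is adequately controlled.
2. **Covariates.** Keep the date-of-birth adjustment in these models, preferably as a flexible term, and make Table 2 agree with the confounding section.
3. **Coding era.** Split each WA child's follow-up at 1 July 1999 and stratify the baseline hazard on coding version. If the recorded hazard is the product of an age effect, a version-specific capture factor and a vaccine effect, each stratum's baseline absorbs its own capture factor. The coding-era bias then goes whatever form the birth-date term takes.
4. **Optional.** Run a sensitivity analysis on ICD-10 AM follow-up only, with delayed entry at 1 July 1999. It discards infancy follow-up of earlier-born WA children, so it should not replace the main analysis.

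The cost is one episode split, one stratum variable and a wording change. Precision falls slightly in the first two years of WA follow-up, the only ages at which both versions coexist.
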